### Randomization and Allocation

The randomization list will be created through the website www.randomization.com and a block randomization will be performed to allow the permutation of the order and size of the blocks. Each patient allocation will be performed using opaque envelopes, sealed and labeled with a random number assigned to the participant. Envelopes tell you if the participant receives active or sham treatment, according to the code on envelope.

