
As the DSM-5 definition of mixed features has been recently published, treatment guidelines that provide recommendations for treating mixed episodes are still limited (42). Some authors suggest that data from clinical trials using mixed episodes defined by DSM-IV-TR may guide the treatment of mood episodes with mixed features defined by DSM-5, but with certain caveats (42). The DSM-IV definition of mixed episodes was restrictive and as such cannot be applied to the current definition of mixed states in DSM-5, with the caveat that the current definition does not yet understand DIP symptoms and that recent studies shows that DIP symptoms are likely to be cardinal symptoms of mixed states (17). In addition, these previous studies were conducted in patients with bipolar I disorder, whose results cannot be applied to mixed states of BD II and MDD (43). Mixed specifier of mood disorders (TB and MDD) are probably a different subgroup in terms of clinical response to treatment, socio-demographic parameters, course (frequency of recurrences, predominant polarity, etc.), and family history (44).

The main objective of this study is to evaluate the efficacy and safety of TBS as an add-on treatment for mood stabilizers (in BD I and II) or antidepressants (in MDD) in moderate and severe major depressive episodes with mixed features. Therefore, TBS will be combined to pharmacological treatments of patients who are adequately treated with first or second-line drugs to treat a mixed depressive episode of either MDD (antidepressants) or BD (mood stabilizers), according to CANMAT, and still present with moderate or severe mixed depression. In addition, the study aims to evaluate the impact of restrictive (without “DIP symptoms”) and broad (considering “DIP symptoms”) criteria on treatment-related factors and other clinical features.

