## Methods

### Design and Study Population

This will be a randomized, double-blind, sham-controlled, 6-week clinical trial, comprising 5 consecutive days a week sessions for the first 3 weeks and then 2 days a week (interval at least 1 day between sessions) for a further 3 weeks of active or sham TBS. The study will be conducted at the Institute of Psychiatry of the School of Medicine of the University of Sao Paulo (HCFMUSP). The study will be conducted in accordance with the principles established by the Declaration of Helsinki (45) and the American Document of Good Clinical Practice (46). This protocol have been published in www.clinicaltrials.gov with the number NCT04123301.

Ninety adult patients aged 18 to 65 years with a diagnosis of type I BD, type II BD or MDD in moderate or severe depressive episode (according to DSM-5 criteria) with mixed features (according to DSM-5 criteria plus symptoms of distractibility, irritability and psychomotor agitation). The diagnosis will be confirmed by the Portuguese version of the structured interview of DSM-IV (Structured Clinical Interview—SCID IV) (47) modified with the DSM-5 criteria and specifiers without the exclusion of symptoms distractibility, irritability, and psychomotor agitation, since there isn't a Portuguese version of the SCID of DSM-5. Recruitment strategies will include referrals from other doctors and advertising at internet and newspapers. Participants will be randomized using a computer generated list for one of two intervention groups (in a 1:1 ratio) to the active or sham TBS group. Allocation masking will be done by sequentially numbered cards that will determine which group each patient belongs to. The card determines whether the coil to be used will produce active or sham stimulation. A person not directly involved in the clinical trial will be responsible for delivering the sham or true coil according to randomization, remembering that the coils are physically identical and have similar sound properties and stimuli. Participants and staff will be unaware of the status of allocation groups.

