### Statistical Analysis

Statistical analyses will be performed using Stata^®^ (67) and the Statistical Package for the Social Sciences—SPSS^®^ (68). The overall significance level for this study will be 0.05 using two-tailed tests. The study results will be analyzed for two patient populations: the intention-to-treat (ITT(and the per-protocol (PP) analysis set. The ITT set will include all subjects who met the study eligibility criteria and received at least one week active/sham TBS treatment. The PP population thus will include all subjects from the ITT set who receive the protocol-specified treatment and complete the 6-week treatment regimen or withdrew before completion per the study protocol. Comparisons of baseline demographic and clinical characteristics and safety assessments will be performed on the ITT analysis set. The primary efficacy analysis will be performed using the PP analysis set.

Comparisons of baseline demographic and clinical characteristics between the study groups will be performed to ensure that the groups are balanced at baseline and that the randomization is successful. For comparison of means (continuous variables), the two-sample t-test or a nonparametric equivalent will be used. For comparison of proportions (categorical variables), the chi-square test or Fisher's exact test will be used, as appropriate. The change in MADRS total score from baseline to week 3 (primary endpoint) will be compared between the treatment groups using a linear mixed model (69) with a continuous dependent variable (MADRS score) to measure the primary outcome. For primary outcome subject will be the random effect and the fixed factors will be intervention (sham × active). Secondary outcomes will also follow the same pattern and the scales' scores will be the random effect and the fixed factors will be intervention (sham × active). Since patients will be taking different medications and dosages, the defined daily dose (DDD) will be used in the statistical analysis. This enables the inclusion of several medications and doses in the model, as medication groups (e.g., antidepressants, anticonvulsants, etc.).

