We are aware that our study has some limitations. The current study will be an add-on TBS study, in spite of the randomized and sham-controlled design. It has been reported that add-on repetitive TMS treatment could enhance the clinical responses to antidepressants (76), therefore, the observed responses to TBS could partly result from modulation of the effects of the medications that patients were using during the TBS treatment. However, before we have solid evidence to support the antidepressant efficacy of TBS, the add-on design is more ethically sounded and could provide more real-life data. The concomitant medications will not be allowed to be changed and will be their original medication regimen which they had failed to respond to. Someone could consider mixed sample (BDI, BDII and unipolar depression) a limitations of the study, however last decade evidence corroborated the change that occurred in the DSM-5 in which the old mood episode called “mixed state” (only allowed in bipolar I disorder) was removed and changed into a mood specifier that can be applied to major depressive episodes of both bipolar I disorder, bipolar II disorder, and MDD (unipolar depression). This change suggests that the major depressive episodes of these diseases are similar in terms of clinical presentation, so much that the specifier “with mixed features” (mixed depression) can be attributed to all of them. The fact that these are different diseases might not affect the treatment of the acute depressive episode, similar to what we observe in antidepressants use to treat acute depression of MDD, bipolar II disorder and even bipolar I disorder (protected by mood stabilizers) (55). Thus, consolidating a recent transdiagnostic approach to psychiatric diseases, our objective is also to verify whether the same clinical presentation (mixed depression) could be treated in the same way with TBS regardless of the diagnosis, since all patients will be in a moderate or severe mixed depression.

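### Allocation is described as a single permuted-block list with no stratification by diagnosis, so the MDD/BD balance between arms rests on chance; stratifying on MDD versus BD would be a cheap improvement

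*Protocol article*

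**What the plan says.** Allocation is described twice in the Methods.

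- Design and Study Population: "Participants will be randomized using a computer generated list for one of two intervention groups (in a 1:1 ratio").
- Randomization and Allocation: one list from a public website is described, and of the method the section says that "a block randomization will be performed to allow the permutation of the order and size of the blocks". Sealed opaque envelopes carry the allocation. No stratification factor appears in either place.

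The sample is diagnostically mixed: "Ninety adult patients aged 18 to 65 years with a diagnosis of type I BD, type II BD or MDD". Expected shares are not given. The Introduction describes TBS as an "add-on treatment for mood stabilizers (in BD I and II) or antidepressants (in MDD"), so background drug class broadly follows diagnosis. The Discussion defends the mixed sample and adds the aim of verifying "whether the same clinical presentation (mixed depression) could be treated in the same way with TBS regardless of the diagnosis".

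On the analysis, the Statistical Analysis section states: "For primary outcome subject will be the random effect and the fixed factors will be intervention (sham × active"). Diagnosis is not named. The section does plan to bring medication into the model as defined daily doses by medication group, and to compare baseline characteristics between arms.

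**The concern.** Blocking a single list holds the arm totals close to equal but does nothing to equalise the arms within a diagnosis. Diagnosis is the feature that the authors themselves expect readers to question, and they answer with a transdiagnostic aim. It is also linked to the background drugs. If the sham arm happened to hold clearly more MDD patients than the active arm, a reader could not tell at sight how much of the pooled difference reflects case mix, and the primary model as written names no term for diagnosis. The planned baseline comparison can show such an imbalance but cannot prevent it, and no consequence is attached to it.

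What is at stake is the credibility of the pooled contrast in one realised trial of 90 patients. The validity of the randomisation is not in question.

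**Working it through.** **Figures in the plan.** The article gives no figure on diagnosis balance, so there is none to reproduce. Its sample size (82 evaluable at 90% power and two-sided 5%, 90 recruited, 45 per arm) is used for two things only: the arm sizes, and an implied effect for scale. How 82 was derived is a separate matter.

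**Assumptions.** The diagnosis shares, the block sizes and any prognostic difference between diagnoses are not in the article and are assumed below.

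**1. Chance imbalance, 45 per arm.** Let m of the 90 patients have MDD, and let a of them fall in the active arm. Then a is hypergeometric, and the between-arm difference in MDD share is (2a − m)/45. Its SD is (2/45) × √[m(90 − m)/(4 × 89)].

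- m = 45: (2/45) × √(2025/356) = 10.6 points. A difference above 10 points needs |2a − 45| ≥ 5, that is a ≤ 20 or a ≥ 25. Probability 0.40.
- m = 30 (or 60, by symmetry): (2/45) × √(1800/356) = 10.0 points. It needs a ≤ 12 or a ≥ 18 when m = 30. Probability 0.26.
- m = 18 (a 20% share): SD 8.5 points, probability 0.19.

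The jump from 0.26 to 0.40 is partly discreteness around the 10-point threshold.

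**2. Simulation of the blocks.** With sizes 4, 6 and 8 (assumed) and 8,000 trials per scenario:

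| MDD share | One list: P(>10 points) | Separate MDD and BD lists: P(>10 points) |
|---|---|---|
| 1/3 | 0.32 | 0.00 |
| 1/2 | 0.35 | 0.00 |
| 2/3 | 0.30 | 0.00 |

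The 95th percentile of the difference is about 20 points with one list and about 3 points with separate lists. The stratified results assume stratification from the first patient.

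**3. Effect on the pooled contrast if diagnosis is not adjusted for.** Shift = imbalance × prognostic difference.

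- With an assumed 5-point difference in MADRS improvement: 0.10 × 5 = 0.5 point, and 0.20 × 5 = 1.0 point.
- In SD units, with an assumed prognostic difference of 0.5 SD and a one-SD imbalance of about 10 points: 0.10 × 0.5 = 0.05 SD.

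For scale, 82 patients at 90% power imply an effect of √(2/41) × (1.960 + 1.282) = 0.72 SD.

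**4. Cost if diagnosis is adjusted for.** With half the sample MDD and a 20-point imbalance, the squared correlation of arm with diagnosis is (0.20/2)²/0.25 = 0.04. The variance inflation is 1/0.96 = 1.042, and power falls from 0.900 to 0.888. Adding diagnosis to the model therefore deals with most of the problem for the pooled test.

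**5. Effect on the transdiagnostic aim.** Take an interaction as large as the whole implied effect (0.72 SD) with N = 82. If half the sample has the diagnosis and the arms are balanced, the standard error is √(4/20.5) = 0.442 and power is Φ(0.716/0.442 − 1.960) = 0.367. The average under unstratified allocation is 0.363. At a one-third share the figures are 0.331 and 0.326; at 20% they are 0.250 and 0.241. Stratification adds 1 percentage point or less.

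**The case against.** The case against is substantial, and most of it stands.

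- *The absence of strata is inferred.* Neither section says that the list is unstratified. The reading rests on the singular list and on silence in a condensed article. This stands. Still, the dedicated section gives the generator, the blocking, the varying block size and the concealment, and a stratification factor would belong there.
- *Unstratified blocked randomisation is valid.* Chance imbalance causes no bias in expectation and is already reflected in the standard error. This stands in full.
- *Drug class is partly handled.* The defined-daily-dose terms by medication group address it in the analysis. This stands for drug class. Dose is not diagnosis, however, and diagnosis is named nowhere in the model. The link between the two is also loose: any suitable first- or second-line regimen is admitted, and the Discussion notes antidepressant use in BD. Stratifying by diagnosis would not guarantee balance on drugs.
- *The transdiagnostic aim is thinly anchored.* It appears in the Discussion only. The Study Hypothesis section and the outcome list specify no comparison within or between diagnoses. This stands.

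A reader might infer two stronger claims. One is that the treatment comparison is biased or confounded by diagnosis; the documents do not support this, for the reasons above. The other is that stratifying would make effects within each diagnosis, or the claim that TBS works alike across diagnoses, properly testable. It would not: interaction power stays at about 25–37% even with perfect balance, and a two-stratum scheme does not balance BD I against BD II.

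**Conclusion.** The point holds as a modest, cheap design improvement and not as a validity flaw. As the article describes it, MDD/BD balance is left to chance and diagnosis is absent from the named model terms. A difference of more than 10 points in MDD share would arise in roughly 26–40% of trials for MDD shares between one third and two thirds, and in about 19% at a 20% share. The likely shift in the pooled estimate is small against the implied effect: about 0.05 SD against 0.72 SD, if diagnoses differ by 0.5 SD. These sizes depend on assumed diagnosis mixes, block sizes and prognostic differences. If the full protocol already stratifies by diagnosis, the allocation part of the point falls away and one sentence in the article's text would settle it.

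**What to change.** Amend Randomization and Allocation to permuted blocks of random size, stratified by MDD versus BD I/II, with a separate list and a separately numbered envelope set for each stratum. Keep allocations already made and use the stratified lists for patients still to be randomised; the Conclusion says that recruitment was not complete at submission. In Statistical Analysis, name diagnosis (the stratification factor) as a fixed effect in the primary model alongside intervention. Two strata are enough, because a further split into BD I and BD II could leave many incomplete blocks.

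The cost is a short amendment, a second list from the same source, a second envelope set and slightly more allocation handling, with possibly one incomplete block per stratum. No patients, visits or staff are added. The balance is weaker the later the change comes. If half the patients were already allocated, their share of the imbalance remains, with an SD of roughly 10.6/√2 = 7.5 points at a 50% MDD share. In that case the diagnosis term in the model does most of the work.

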### Intervention

TBS sessions will be performed using MagPro X100 TMS device (Magventure, Lucernemarken, Denmark) and Cool-B65 A/P (Magventure, Lucernemarken, Denmark) coil. An identical butterfly coil for both active and sham stimulation will be used. The coil will be positioned over the DLPFC and the cortical location will be obtained through anatomical measurements (F3 and F4 positions determined by the 10–20 Electroencephalographic International System) on the right and left. As most mixed depressive episodes are resistant to drug treatment and there are no clinical trials evaluating TBS specifically in mixed depressive episodes so far, we replied a study protocol (41) that evaluated TBS in resistant major depressive episodes of MDD. The bilateral TBS sections will be applied in the following order: first inhibitory stimulation—cTBS—in the right DLPFC followed by excitatory stimulation—iTBS—in the left DLPFC with the following parameters: in cTBS bursts of three pulses at 50 Hz (20-ms interval between stimuli) will be applied continuously for 120 s totaling 1800 pulses in the right DLPFC and iTBS bursts of three pulses at 50 Hz (20-ms interval between stimuli) will be applied for 2-s duration repeated every 10 s for a total time of 570 s also totaling 1800 pulses in the left DLPFC, both with 80% of visual motor threshold (64). We will use a magnetic stimulator device (MagVenture^©^, United States) in study mode for double-blind trials. Participants will perform one session a day over five consecutive days (Monday to Friday) at the first, second and third weeks and then sessions 2 days a week, with an interval of at least 1 day between sessions, for a further 3 weeks of active or sham TBS.

### Blinding

As this is a double-blind study, both the investigators who will perform the clinical evaluations, the researchers who will perform the TBS sessions, and the participants will not be aware of the treatment given to each participant until the end of the study.

### Sample Size Calculation

There are no studies on mixed depression using neuromodulation techniques, so that we used a study that used a similar methodology (bilateral TBS) (41) for treatment-resistant unipolar depression that found a reduction of 52.5% of the depression scale for the active group and a reduction of 17.4% of the depression scale for sham group (F/X^2^ = 6.166). The sample size calculation took into account this measure of effect size obtained in the study cited and was performed with Stata^®^ Statistical Software. The total number of participants we calculated was 82 participants, taking into account 90% power and 5% alpha. As this is a long term study we estimate a dropout rate of 10%, similar to recent studies in this field (37). Thus, we will need to recruit 90 patients, 45 participants in each group (active versus sham).

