Repetitive transcranial magnetic stimulation (rTMS) is widely known treatment option for MDD (31). A recent rTMS meta-analysis in the treatment of depressive episodes indicates that the technique yields statistically significant results improving 30% of patients receiving active excitatory rTMS compared to 10% of patients receiving sham treatment (analysis based in 29 randomized, double-blind, and controlled clinical trials) (32). Recently, a new form of rTMS, the theta-burst mode stimulation (TBS) was introduced and appears to produce at least similar effects on brain activity than standard rTMS (33–36). In addition to greater efficacy, the reduced duration of administration may be another advantage of TBS compared to conventional rTMS procedure, standard TMS sessions last about 45 min, whereas TBS requires less than 10 min of stimulation (33, 37). There are two types of TBS stimulation: intermittent (iTBS) and continuous (cTBS), with facilitating and inhibitory effects, respectively (36). Recent evidence is growing about TBS use in treatment resistant depression (38). Despite the growing number of studies on BD neuroimaging in recent years, the brain regions involved in mood dysregulation in episodes with mixed features have been poorly studied. If some neurofunctional abnormalities appear to be independent of mood state, others appear to be preferentially associated with mania or depression involving the amygdala and other limbic regions, as well as frontal ventral regions, with possible hemispheric lateralization of these anomalies according to mood state patient (36). The few mixed state neuroimaging studies so far support the hypothesis of lateralization of brain abnormalities in relation to bipolar symptomatology, suggesting that neurofunctional abnormalities preferably located in the frontal and limbic areas of the right hemisphere may be associated with the depressive component whereas abnormalities similar left regions would be associated with the manic component (39). Few studies have evaluated the efficacy of TMS in mixed depressive states alone. A recent open study has shown that low frequency (inhibitory) of repetitive (non-TBS) TMS on the right dorsolateral prefrontal cortex (DLPFC) for 3 weeks led to a response and remission rate of 46% and 28%, respectively, in depressive episodes with mixed features of type I BD (40). On the other hand, a study with TBS modality showed that bilateral stimulation (right cTBS and left iTBS) produced greater results in treating major depressive episodes of MDD than unilateral stimulation (41).

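### The 82 participants and 90% power rest on a test statistic and percent reductions without an SD, neither of which is an effect size, so the power claim is tied to no stated difference

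*Protocol article*

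**What the plan says.** The Sample Size Calculation section borrows its planning figures from a trial of bilateral TBS in treatment-resistant unipolar depression, which "found a reduction of 52.5% of the depression scale for the active group and a reduction of 17.4% of the depression scale for sham group". The figure F/X² = 6.166 follows in parentheses. The section continues: "The sample size calculation took into account this measure of effect size obtained in the study cited". It then gives the result: "The total number of participants we calculated was 82 participants, taking into account 90% power and 5% alpha". After assuming 10% dropout it ends with "Thus, we will need to recruit 90 patients, 45 participants in each group (active versus sham").

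The Statistical Analysis section supplies the sidedness: "The overall significance level for this study will be 0.05 using two-tailed tests". It plans a linear mixed model for MADRS change to week 3, a continuous endpoint.

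The section justifies borrowing from unipolar depression by stating: "There are no studies on mixed depression using neuromodulation techniques". The Introduction, however, reports one: "A recent open study has shown that low frequency (inhibitory) of repetitive (non-TBS) TMS" gave 46% response and 28% remission in bipolar I depressive episodes with mixed features.

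**The concern.** An effect size for a continuous endpoint is a mean difference with its SD, or the ratio of the two. An F or chi-square value is not one: for the same true difference it grows with the number of patients in the study that produced it. Two mean percent reductions give a difference of 35.1 percentage points but no spread, so they do not fix a standardised difference either. Whichever of the two the section means, the reader cannot tell what MADRS difference the trial has 90% power to detect.

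The sample size and its power are what a reader relies on when interpreting the result, especially a null one. The recruitment figure derived from 82 also falls slightly short of 82 after the stated dropout.

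**Working it through.** **Inputs stated in the article.** Alpha 5%, two-sided; power 90%; 1:1 allocation; 52.5% versus 17.4% reduction; F/X² = 6.166; 82 required; 10% dropout; 90 recruited. The Discussion gives the cited study's total as 60.

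**Inputs not stated.** SD, mean MADRS difference, standardised difference, degrees of freedom, and the number and size of the cited study's arms. The Introduction says that study also compared bilateral with unilateral stimulation, so its 60 patients need not have been split into two groups.

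**Step 1: can 82 be reproduced?** Not from the stated inputs. Solving backwards for 41 per arm:
- normal approximation: d = (1.960 + 1.282) × √(2/41) = 0.716
- noncentral t: d = 0.725

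On the 35.1-point difference (52.5 − 17.4), d = 0.725 implies an SD of 35.1/0.725 = 48.4 percentage points. Neither figure appears in the article.

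**Step 2: F read as a two-group statistic.** With n per arm in the cited study, d = √(6.166 × 2/n). Because n is not given, it is varied as an assumption. N and power are from the noncentral t, two-sided 5%.

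| Assumed n per arm, cited study | d | Total N for 90% power | Power at 82 |
|---|---|---|---|
| 15 | 0.907 | 54 | 98% |
| 20 | 0.785 | 72 | 94% |
| 25 | 0.702 | 88 | 88% |
| 30 | 0.641 | 106 | 82% |

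The same F supports an N from 54 to 106, on either side of 82. This is the practical consequence of using a test statistic as the input.

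**Step 3: the percentages read as response proportions.** At 90% power, two-sided, the total N is 68 (unpooled), 74 (pooled or arcsine), 86 (continuity-corrected) or 84 (Fisher exact, with 89.6% power at 41 per arm). Fisher exact comes close to 82, but it treats mean percent reductions as responder rates, while the endpoint is continuous.

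**Step 4: dropout.**
- 82 × 1.10 = 90.2, which matches the stated 90. The article does not say how dropout was added, so this route is an inference.
- Retaining 82 after 10% loss needs 82/(1 − 0.10) = 91.1, hence 92 at 1:1.
- 90 × 0.90 = 81.
- If 41/41 gives 90.0% power (d = 0.725), 41/40 gives 89.6%.

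**Step 5: the premise about earlier studies.** The Introduction's study is repetitive TMS in depression with mixed features, which is neuromodulation in mixed depression. The Intervention section makes the narrower claim that no trial has evaluated TBS specifically in such episodes. The two narrower statements agree with each other; the broad sentence in the sample size section does not fit them.

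**The case against.** The strongest reply is that the phrase about effect size may refer to the two percentages, with F printed only as a supporting figure, and that the SD entered in Stata may sit in a full protocol that a journal article condenses. The ambiguity is real. It does not rescue the passage: the article chose to print a derivation, and neither candidate input is an effect size for the MADRS endpoint.

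A second reply is that the range in the table depends on arm sizes the documents do not give, and that 20 and 25 per arm bracket 82. That is correct. A reader might infer from the 106, or from the 82% power, that the trial is underpowered. The documents do not support this, because other assumed arm sizes give power well above 90%.

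A third reply concerns dropout. A reader might infer that the shortfall to 81 is what undermines the 90% power. It does not: it is one patient and 0.4 percentage points. The article also gives 82 as the number calculated, not as the number expected to remain. Nor is every dropout necessarily lost to the primary analysis: the endpoint is at week 3 of 6, MADRS is taken weekly to week 3, the analysis is a mixed model, and the per-protocol set keeps some patients who withdraw early. So 81 is what the plan's own 10% leaves, not an established analysed number.

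Finally, the sentence about no earlier studies has no effect on N. The contradicting study was open and did not use TBS, so it offered no sham contrast to plan from. It is a wording slip and carries little weight here.

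**Conclusion.** The point holds in a limited form. The article labels as an effect size something that is not one, and as a result the claim of 82 patients and 90% power cannot be tied to any difference in MADRS. Power at 82 runs from 98% down to 82% across assumed arm sizes of 15 to 30 in the cited study, so the claim is unsupported but not shown to be wrong. The dropout slip is separate and minor (92 needed instead of 90, or 81 left instead of 82).

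These figures assume a two-sample t-test at two-sided 5% with 1:1 allocation. The planned mixed model could give somewhat different power, depending on correlations the article does not state.

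**What to change.** 1. Stop presenting F/X² = 6.166 as an effect size.
2. State the MADRS difference and SD (or the standardised difference) actually entered in the Stata calculation, and recompute N and power from it. If that input cannot be recovered, say that 82 gives 90% power for a standardised difference of about 0.725 and label this as back-calculated. It should not be printed as though it had been the planning assumption.
3. Keep 90 recruits but state that 10% dropout leaves 81, with the resulting power (about 89.6% if 82 gives 90.0%).
4. Narrow the sentence on earlier studies to the absence of TBS trials in mixed depression, in line with the Introduction and the Intervention section.

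Power for smaller standardised differences could be added but is optional. The cost is rewording and one recalculation; restating the evaluable number needs no extra patients. If the recovered input gives power other than 90%, that power should be reported.
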